Although the treatment with artesunate compared to quinine considerably reduces mortality in severe and cerebral malaria, the case fatality rate remains high at between 20% and 30%[[1]](#endnote-2). Improved supportive care can importantly further reduce mortality; a series from a well equipped intensive care unit in Paris showed a mortality of 11% in patients with severe malaria[[2]](#endnote-3). Supportive treatments include highly technical aids like renal replacement therapy and mechanical ventilation, but also easier to achieve treatments like enteral feeding. In the well equipped intensive care setting early start of enteral feeding in a wide variety of patients, including those with sepsis, is now common practice. Nutrition supplies vital cell substrates, antioxidants, vitamins, and minerals, essential for normal cell function. Studies have shown that early enteral feeding preserves the barrier function of the gut, has positive effects on immune functions, is associated with a decrease in hypermetabolism and organ failure, and reduces the chance of bacteraemia [[3]](#endnote-4) [[4]](#endnote-5) [[5]](#endnote-6) [[6]](#endnote-7) [[7]](#endnote-8) [[8]](#endnote-9). In severe malaria, patients are often poorly nourished and hypoglycaemia is a common complication, especially in patients receiving quinine. Also, bacteraemia with Salmonella species is more common in severe malaria[[9]](#endnote-10), associated with increased bacterial translocation in the gut. Enteral feeding might have a beneficial effect here. The downside of starting enteral feeding in the dependent comatose patient is the risk of aspiration pneumonia; this risk is also present in the mechanically ventilated patient[[10]](#endnote-11) [[11]](#endnote-12), although the risk is lower with the use of post-pyloric enteral feeding tubes[[12]](#endnote-13) [[13]](#endnote-14) [[14]](#endnote-15). A supine position of the patient is a risk factor[[15]](#endnote-16). Routine endotracheal intubation to protect the airway in comatose malaria patients is not a feasible option in most of the tropical countries where malaria is endemic. The use of enteral feeding through a naso-gastric (NG) tube might thus induce a much higher risk of aspiration pneumonia, outweighing the theoretical benefits.

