At Chittagong Medical College Hospital (CMCH), the current practice is to start early enteral feeding through a NG-tube, with a volume of 2-4ml/kg per feed every 2 hours, avoiding 2 late night feeds, resulting in a total of 10 feeds per day for adults. For children fluid supplementation is as follows: for age 2-4years: 100 - 120ml/kg/day; 4-8yrs 90-100ml/kg/day; 8-12yrs 70-90 ≥12 yrs 60-70ml/kg/day given every 2 hours round-the-clock. In both the cases the enetral feeding volume is derived from total volume subtracting the volume given as i.v. fluids. The feeds are prepared from locally available food by blending or commercially available powder form. Although not formally assessed, aspiration pneumonia is a rather common complication of NG feeding in CMCH. Factors that can contribute include the supine position of the patient and no check for gastric retention before the next feeding. We here propose a randomized trial to compare the start of early versus late nasogastric tube feeding, with aspiration pneumonia, incidence of hypoglycaemia and coma recovery times as primary outcome measures.

Materials and Methods

*Place and Period of Study*

It is planned to study 124 consecutive patients, age 2 y/o, with cerebral *Plasmodium falciparum* malaria, defined as a Glasgow Coma Score (GCS) below 11or BCS <3 (for pre-verbal children) and the presence of asexual stage *P. falciparum* parasites in a peripheral blood slide, admitted to Chittagong Medical College Hospital, Chittagong, Bangladesh. Patients will be recruited from the internal medicine wards (ward 13, 14, and 16) and from the paediatric ward.

*Inclusion Criteria*

1. Cerebral falciparum malaria defined as a GCS<11or BCS <3 (for pre-verbal children), and the presence of asexual forms of *P. falciparum* in the peripheral blood smear.
2. The attending relative able and willing to give informed consent.
3. ≥2 years of age

*Exclusion Criteria*

1. Relatives unable or unwilling to give informed consent.
2. Patients who already have the features of aspiration pneumonia.
3. Pregnancy
4. Diabetic requiring insulin
5. Contraindications to enteral feeding:

-Circulatory shock

-Mechanical bowel obstruction / ileus / ischaemic colitis (redcurrant jelly stools)

-Severe diarrhea (> 6 per 24 hours), severe vomiting (> 6 per 24 hours) or severe dehydration due to either

-Pancreatitis (laboratory confirmed: serum amylase >500 U/L)

6. Known allergies to artesunate or quinine

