7. Severely malnourished child (according to WHO criteria)

*Examination and Treatment*

On enrolment a full history and physical examination will be carried out. Nutritional status of the patient will be assessed by skin-fold thickness in the triceps region of the left arm and the mid upper arm circumference will be measured. Weight/height and presence of bilateral pedal edema (WHO criteria) for malnourished children will be assessed.

First line antimalarial treatment will be with intravenous artesunate, if available. Artesunate (Guilin No 2 Pharmaceutical Factory, Guangxi, Peoples’ Republic of China) will be given in a dose of 2.4 mg/kg body weight on admission, then at 12 hours, 24 hours, and thereafter once daily until oral medication can be taken reliably. Each 60 mg vial contains anhydrous artesunic acid which is dissolved initially in 1 ml 5% sodium bicarbonate and then mixed with 4 ml of 5% dextrose before injecting as a bolus into an indwelling intravenous cannula. When the patient has recovered sufficiently to take tablets, a full adult course of artemether-lumefantrine (CoartemR) will be given: 4 tablets twice daily for 3 days. Currently injectable artesunate is not registered yet in Bangladesh for the treatment of severe malaria. In case artesunate for injection is not available, the patient will be treated with i.v. quinine. A loading dose of 20 mg/kg will be given over 4 hours time followed by a dose of 10 mg/kg over 2 to 4 hours every 8 hours for a total of 7 days, or until the patient has recovered sufficiently to take tablets, in which case a full course of coartem will be given (see above). Patients will be managed in accordance with the World Health Organization guidelines 2006.

*Treatment allocation*

All patients will receive a NG tube. Patients will be randomized to either receive enteral feeding upon admission through the NG tube *(arm 1)*, or no feeding until able to take oral food or maximum until 60 hours (adults i.e. >12 years old) or 36 hours (children i.e. <12 years old) after admission followed by enteral feeding *(arm 2)*. The feed used in the study will be Revit-R/Renovit(patient with renal insufficiency) (Fasska SA, Louvain la Neuve, Belgium. The preparation comes as a powder, which will be dissolve in bottled water according to the instructions of the manufacturer (220g per liter water which will provide 1 kcal/ml) The feeding protocol is as follows:

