Aspiration pneumonia will be diagnosed clinically from history and chest examination (fever, respiratory distress, auscultatory crackles, oxygen saturation), and confirmed by chest X-ray (CXR). All patients will have a CXR upon admission. If possible, a CXR will be done in the radiology department of CMCH. If the patient is not transportable, a bed side CXR will be performed. The CXR will be repeated upon indication and 3 days after the first one for follow-up. Treatment will be with antibiotics (intravenous ceftriaxone in combination with metronidazole). Oxygen will be given by nasal cannula or face mask where indicated. In the case of severe respiratory insufficiency, a concerted effort will be made to transfer the patient to the intensive care unit of CMCH for mechanical ventilation.

Analysis

*Primary outcome measures include:*

1. Incidence of aspiration pneumonia.
2. Incidence of hypoglycaemia (<2.2 mmol/L).
3. Coma recovery time. The coma recovery time is defined as the time till a Glasgow Coma Score of 15/15 (BCS 5/5 in preverbal children).

*Secondary outcome measures include:*

1. Incidence of sepsis.

Sepsis is defined as the presence of infection (other than malaria) in combination with systemic inflammatory response syndrome (SIRS) as indicated by ≥ 3 of the following criteria: prolonged fever i.e. axillary temperature  38ºC or core temperature of  36ºC; a heart rate of  90 beats/min; a respiratory rate of  20 breaths/min (up to 5yrs 40) or the use of mechanical ventilation for an acute respiratory process; a white-cell count of  12 x 109/l or  4 x 109/l, or a differential count showing > 10% immature neutrophils.

2. Time to sit independently, which will be assessed daily.

3. Time to speak independently, which will be assessed daily.

4. Time to eat independently, which will be assessed daily.

5. Total duration (days) of admission in the hospital.

6. Survival. In hospital mortality will be recorded.

Sample size calculation

To detect an increase in incidence in aspiration pneumonia from 10% to 30%, a sample size of 124 (62 in each treatment group) is required. After this pilot study the data will be analysed. If early enteral feeding appears to be promising regarding a decrease in hypoglycaemia or a shortening of coma recovery times, not at the expense of a significant increase in aspiration pneumonia, a larger follow-up trial will be planned.

Randomisation

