Randomisation will be balanced in blocks of 20 by computerized method using STATA statistical software package.

Safety

Current practice in CMCH is to start on the day of admission with enteral feeding. However, if the current study shows a significant increase in the incidence of aspiration pneumonia in the group receiving early enteral feeding, randomization will be stopped, and patients will only receive enteral feeding after regaining consciousness, or 60 hours after admission. Since aspiration pneumonia is an identified risk, interim analyses will be performed after every 50 patients included. Interim data will be analysed by the Data Safety Monitoring Committee.

Benefits of the study

There is currently equipoise about the benefit of the start of early enteral feeding in patients with cerebral malaria in the tropical setting. Theoretical advantages (prevention of hypoglycaemia, restoration of immune function, etc) are countered by the increased risk of aspiration pneumonia. The study has a clear practical goal to guide this important part of the treatment of patients with cerebral malaria.

Finance

Costs involved in the study will be financed by the Wellcome Trust of Great Britain

References

1. SEAQUAMAT study group. Artesunate versus quinine for treatment of severe falciparum malaria: a randomised trial. Lancet 2005; 366: 717-725 [↑](#endnote-ref-2)

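### Randomisation in blocks of 20 names no stratification factor; separate adult and paediatric lists, with an analysis adjusted for age group and antimalarial, would be a cheap gain in balance and precision

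*Protocol*

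**What the plan says.** The Randomisation section of the protocol reads: "Randomisation will be balanced in blocks of 20 by computerized method using STATA statistical software package". It names no stratification factor and does not give the number of lists.

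Other sections show that the trial population is mixed in two respects.

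- **Age group.** Under Place and Period of Study: "Patients will be recruited from the internal medicine wards (ward 13, 14, and 16) and from the paediatric ward". Under Treatment allocation, feeding in arm 2 is withheld until oral food is possible or "maximum until 60 hours (adults i.e. >12 years old) or 36 hours (children i.e. <12 years old) after admission". The feeding protocol gives adult controls 5% glucose-saline, put at 10-12 kcal/kg per 24 hours. Paediatric controls get 10% dextrose in half-strength saline, put at 36-48 kcal/kg for ages 2 to 8. Adults have 10 feeds a day and children 12, with different definitions of gastric retention.
- **Antimalarial.** Artesunate is first line, but "In case artesunate for injection is not available, the patient will be treated with i.v. quinine". The Background says that in severe malaria "hypoglycaemia is a common complication, especially in patients receiving quinine".

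The three primary outcomes are aspiration pneumonia, hypoglycaemia and coma recovery time. On size, the protocol says: "To detect an increase in incidence in aspiration pneumonia from 10% to 30%, a sample size of 124 (62 in each treatment group) is required".

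**The concern.** Blocking keeps the two arms close in size. It does not keep them alike in the share of children, because children and adults arrive mixed within a block. The protocol's own figures make age group worth balancing. Between ages 2 and 8, control patients receive 3 to 4.8 times the adult glucose energy per kg (36/12 to 48/10), and one primary outcome is low blood glucose. The antimalarial is worth accounting for because the protocol itself links quinine to that same outcome.

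If the arms differ in either factor, part of an observed difference in hypoglycaemia may reflect the mix of patients and not the feeding policy. With about 62 patients per arm, and a decision on a larger trial resting on the result, that would make the result harder to interpret. The allocation scheme is protocol content, so this does not depend on what an unseen SAP may contain.

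**Working it through.** **1. The plan's own figure.** The documents give 10% and 30%, but no alpha or power. Assume two-sided 0.05, 80% power and a pooled variance, so the mean proportion is 0.20:

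n per arm = [1.960·√(2·0.2·0.8) + 0.842·√(0.1·0.9 + 0.3·0.7)]² / 0.20² = 61.6, rounded up to 62.

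The stated 124 is reproduced. Stratifying does not change it.

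**2. Chance gap without stratification.** Let f be the share of patients with the factor. The documents do not give f for children or for quinine, so a range of 10% to 50% is assumed. The standard deviation (SD) of the between-arm difference in that share is about √(2f(1−f)/62). For f = 0.3 this is √(0.42/62) = 0.082, or 8.2 points. The other columns come from simulating 124 patients in permuted blocks of 20.

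| Share f | SD by formula (points) | Simulated chance of a gap ≥10 points | Simulated chance of a gap ≥15 points |
|---|---|---|---|
| 10% | 5.4 | 6% | 0.5% |
| 20% | 7.2 | 16% | 4% |
| 30% | 8.2 | 22% | 7% |
| 40% | 8.8 | 24% | 8% |
| 50% | 9.0 | 24% | 9% |

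A normal approximation gives slightly more at the upper end (26% at a 40% share, for 10 points) because it ignores that counts are whole numbers.

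**3. The same with separate lists, still in blocks of 20.** The SD of the gap falls to between 2.0 and 3.1 points. The chance of a gap of 10 points or more is 0.1-0.2% at a 10% share and about 0.01% or less from 20% upward.

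**4. What a gap does to the result.** Shift in the crude risk difference = gap × difference in risk between the two kinds of patient. The documents give no such risk difference, so 10 to 30 points is assumed. A 15-point gap then shifts the result by 0.15×0.10 = 1.5 to 0.15×0.30 = 4.5 points. At one SD for f = 0.4 and a 20-point risk difference, the shift is 0.088×0.20 = 1.8 points. For scale, at an assumed hypoglycaemia rate of 10% to 30% the standard error of the arm difference is √(2·0.1·0.9/62) = 5.4 to √(2·0.3·0.7/62) = 8.2 points.

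**5. Quinine given in one spell.** The protocol makes quinine depend on the supply of artesunate. If its use falls in one continuous run of patients (25, 37 or 62 of the 124 were tried), the time-ordered blocks already balance most of it: SD about 4.3 points and about a 2% chance of a 10-point gap.

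**6. Cost in arm sizes.** One list of 124 in blocks of 20 gives arms of 60 to 64. With two lists, each may end in an incomplete block; in simulation an arm held 58 to 66 patients in about 99% of runs.

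**The case against.** Several arguments against the point carry weight.

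- **Validity.** Unstratified blocking is a legitimate choice, above all in what the protocol calls a pilot. Chance imbalance is random error that the standard error already covers. A reader might infer that the comparison is biased; it is not.
- **One list.** A reader might infer that a single list is prescribed. The text is silent, and a list per ward is not ruled out. What can be said exactly is that no stratification factor is named.
- **Strength of the factors.** A reader might take age and drug to be strong predictors of outcome. The documents give no rates. They link quinine to hypoglycaemia in words only, and for age they show different regimens, not a different baseline risk. Different regimens may also mean that the feeding effect differs by age, which stratified randomisation does not resolve.
- **Quinine.** If use follows supply, blocks balance most of it (step 5), so stratifying the randomisation by drug is not called for.
- **Block size.** Stratifying often prompts smaller blocks. Tube feeding is visible at the bedside, so smaller fixed blocks would make the next assignment easier to guess. Step 3 shows that blocks of 20 are enough.
- **Analysis detail.** Adjusted and subgroup analyses may sit in an SAP that is not shown, so their absence from the protocol is not itself a fault.

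What remains is that the protocol fixes the allocation scheme without a factor that it treats differently throughout and that the wards already separate.

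**Conclusion.** This is a cheap improvement to a valid design, not the correction of an error. No stratification factor is named, and for an assumed 10% to 50% share of children the chance of a between-arm gap of 10 points or more is about 6% to 25%, against about 0.2% or less with separate lists.

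The effect on the result is moderate. Under an assumed risk difference of 10 to 30 points, a 15-point gap moves the crude difference by 1.5 to 4.5 points, below its standard error, and a gap that large has at most about a 9% chance. The case is firmest for age group. For the antimalarial, adjustment in the analysis is sufficient. These sizes rest on assumed shares and risk differences; the lack of a named factor and the different regimens are stated facts.

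**What to change.** In the Randomisation section, state that allocation uses separate adult and paediatric lists, each in blocks of 20. Define the strata by the same rule that decides which regimen a patient receives. As worded, a patient aged exactly 12 falls in neither group for the maximum delay, so that boundary must be reconciled first.

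In the Analysis section, or in the SAP with a reference from the protocol, state that the primary outcomes will be analysed stratified by age group and adjusted for the antimalarial started at admission, with the drug recorded before allocation. A Mantel-Haenszel risk difference would serve for the two incidences and a stratified Cox or log-rank analysis for coma recovery time.

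The cost is one extra list, one or two sentences, and one possibly incomplete block per stratum. The sample size does not change. If randomisation has begun, leave the scheme as it is and adopt the adjusted analysis alone, before outcomes are examined by arm.
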